### Role of the community health worker

The CHW functions as both an outreach worker and practice facilitator. S/he uses the patient registry to identify patients who are unscreened and implement outreach either mailing out letters or responding to phone calls to patients, and mailing out FOBT kits to unscreened patients. S/he functions as a practice facilitator by working with each practice to implement a tailored system for reminders to patients and clinicians, and also to facilitate referrals of patients who request them for mammography or colonoscopy.

### Preliminary data

In 2009, we piloted the intervention using the eligibility criteria described above. In the mammography arm, 270 women met eligibility criteria for enrollment and 323 men and women met eligibility criteria for enrollment in the CRC arm. The sample was middle aged (22% 40-49 years, 48% 50-59 years, and 29% 60 years and older) and 70% female. Distribution of race/ethnicity was 61% White, 28% Black, 5% Hispanic, and 5% Asian. Health insurance distribution was 42% private (including supplemental private insurance for Medicare), 25% Medicaid, 23% Medicare only, and 9% uninsured.

For the pilot study (but not for the main study) patients were assigned to early v. delayed intervention based on their medical record number. The characteristics of the two groups were similar. The pilot results are notable in two respects. First, patients who were past due had very low rates of screening in the subsequent 12 months. Second, rates of screening were three times higher in the intervention compared to the control group. Because the patients were not randomized, but inadvertently assigned based on medical record number, we conducted a logistic regression model to predict screening that controlled for participant characteristics. These adjusted results from the pilot were similar to our crude results from the pilot study (Odds Ratio 3.63; 95% CI 2.35- 5.61) for having any screening.

### Sample Size determination

For the main study, based on the size of the recruited practice and screening rates from the pilot study, we estimate that 190 patients will be past due for mammography and 239 will be past due for CRC screening. Based on our pilot data, we anticipate rates of screening of 18% and 10% respectively in the usual care (delayed group). Based on our pilot data, we conservatively estimate that this multimodal intervention will double screening rates for both mammography and CRC screening among those in the early intervention group. Based on these assumptions, we will have a minimum of 80% power to detect a difference of 18% in the mammography group and 13% in the colorectal screening group using 95% confidence intervals.

### Patient accrual and study flow

Patient flow for the main study is shown in figure 1. Of the 525 women 40-75 years and men 50-75 years of age that had a visit during the past two years, 148 had undergone timely cancer screening. Of these and 10 were deemed higher risk and not eligible for randomization. A total of 367 patients will be randomized to the two groups.

### Planned analytic approach

Intervention vs. control groups will be compared based on intention-to-treat. That is, once randomized patients will be included in the analysis regardless of whether they leave the practice or not. We will use Generalized Estimating Equation models to control for covariates and clustering within practices. We also will assess whether expected baseline differences in screening by race, ethnicity and insurance are attenuated in the intervention group. We will use a difference in difference approach to assess whether the differences between Whites and Blacks, Hispanics and non-Hispanics, and insured and uninsured patients are significantly smaller in the intervention (early) compared to usual care (delayed group).

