## Methods/Design

### Study design

We use a pragmatic, randomized controlled trial to evaluate this multimodal intervention with the patient as the unit of randomization. This allows for direct comparison of cancer screening rates (intervention vs. control groups) among patients who at the outset are past due for mammography or colorectal cancer screening. We chose to randomize at the patient level rather than physician or physician group level because it is difficult to ensure comparability when randomizing relatively small numbers of physicians or physician groups. It should be noted that patient-level randomization allows for physician learning effects, which bias results towards the null so results from this trial may be conservative.

The study design is shown in Figure 1. Individual patients are randomized and receive the 6 month intervention. Twelve months following randomization the delayed group also receives intervention. The primary analysis will be based on comparison of screening rates of patients in the early group who receive the intervention with those in the delayed group who receive usual care during the same time period. To account for lags between referral and completion of screening, rates of screening will be compared over 12 months.

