### Selection of practice site

We recruited one large safety net practice in Rochester, NY to participate in this trial. Given our aim of evaluating the impact of this multimodal intervention on disparities in cancer screening, we targeted a practice that serve large numbers of low-income and minority patients.

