### Participant consent, eligibility and randomization

The study was approved by the Institutional Review Board of the University of Rochester. Participant informed consent was waived by the Institutional Review Board because the study poses no greater risk to participants than that associated with routine care, participants are free to ignore in-reach or outreach and may request that they receive no further reminders at any time.

Participant eligibility criteria for enrollment in the study include: (1) being a registered patient at the practice (we used a single download from the health system to create a practice registry); (2) having at least one visit to the practice in the past two years (to ensure participants were actively receiving care at the practice); (3) being ages 40-75 years for mammography screening, and 50-75 years for CRC screening; (4) being past due for annual mammography or CRC screening [(recommended intervals are 10 years for those screened through colonoscopy, 5 years for those screened with sigmoidoscopy and/or barium enema, and annually for those screened through fecal occult blood tests (FOBT)]. Women ages 50-75 could be enrolled based on either or both mammography and CRC criteria. Patients at higher risk for cancer due to prior cancer, premalignant conditions, inadequately evaluated breast mass, or positive FOBT were not randomized. Higher risk patients were excluded from randomization due to ethical concerns; clinicians were notified if chart review revealed they were overdue for screening.

Potentially eligible participants were identified using practice billing data based on age, sex and last visit to the practice. These data, in addition to race, ethnicity, presence and type of insurance, name of the primary care physician, and contact information were imported into a secure, customized patient tracking registry that was created in Microsoft Access^®^. Last dates of screening were determined through manual review of the electronic medical record (EMR) by research assistants using structured abstract forms to determine if, when and how participants were last screened.

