### Description of the intervention

The intervention, referred to as "Get Screened," builds on the finding that multimodal initiatives are more powerful for promoting use of preventive services[30]. We use paper prompts that are delivered to the clinician and patient immediately prior to the visit by office medical assistants. No more than three prompts are delivered for the same patient. One research assistant uses the EMR to indentify unscreened patients in the intervention group who have impending visits in during the week. She organizes patients by day of week into an accordion folder and delivers this to each suite within the large practice.

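### The GEE model is meant to control for clustering within practices, but the trial has one practice, so the named cluster level has no replicates

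*Protocol article*

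**What the plan says.** Under Planned analytic approach, the article commits to intention-to-treat and then states: "We will use Generalized Estimating Equation models to control for covariates and clustering within practices". No other regression model is named for comparing the early and delayed groups.

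Under Selection of practice site it says: "We recruited one large safety net practice in Rochester, NY to participate in this trial". Other sections agree that the main study has one practice. The sample size is "based on the size of the recruited practice and screening rates from the pilot study", and the research assistant sorts the prompts into a folder and "delivers this to each suite within the large practice". The design is a trial "with the patient as the unit of randomization", and under Patient accrual and study flow: "A total of 367 patients will be randomized to the two groups".

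Two lower levels of grouping appear in the article but are not tied to the model. The registry imports the "name of the primary care physician". A patient may also qualify for both tests: "Women ages 50-75 could be enrolled based on either or both mammography and CRC criteria".

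**The concern.** A GEE analysis handles correlation by treating clusters as the independent units and estimating the variance from differences between them. If the cluster is the practice and there is one practice, there are no differences to learn from. The article does not leave the cluster level open for a later document; it names one, and that level cannot work in the design it describes.

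At stake is pre-specification of the confidence interval and p-value for the comparison that Study design calls primary. An analyst who follows the sentence literally must abandon it at the first fit. The replacement (clinician, suite, patient or no clustering) would then be chosen with outcome data in hand.

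**Working it through.** **1. The plan's own figures.** Sample Size determination claims at least 80% power for 18 points on 18% (190 patients) and 13 points on 10% (239 patients). Assuming 1:1 allocation and a two-sided 5% test, power = Φ{[d√n − 1.96√(2p̄(1−p̄))] / √[p₀(1−p₀)+p₁(1−p₁)]}, with n per arm and p̄ the mean of p₀ and p₁.
- Mammography, 18% v 36%, n = 95: (1.754 − 1.231)/0.615 = 0.852, power 80.3%.
- Colorectal, 10% v 23%, n = 119.5: (1.421 − 1.029)/0.517 = 0.759, power 77.6% (78.5% with unpooled variance).

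These come from a plain two-proportion calculation with no design effect. They match the claim for mammography and fall slightly short for colorectal screening. The shortfall has nothing to do with clustering.

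**2. The sandwich variance with one cluster.** For K clusters the robust variance is A⁻¹(Σₖ UₖUₖ′)A⁻¹, where Uₖ is cluster k's contribution to the estimating equation and the estimate solves Σₖ Uₖ = 0. With K = 1 the sum is U₁ alone, so U₁ = 0 at the solution. The middle term is 0·0′ and the variance is zero. This holds for any data, any covariates and any working correlation.

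**3. Numerical confirmation.** One simulated data set with 95 patients per arm, true rates 18% and 36%, binomial GEE with logit link; the estimated log odds ratio was 0.691 under independence.

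| Cluster | Standard error of the log odds ratio |
|---|---|
| One practice, robust, independence | 5.5e-17 |
| One practice, robust, exchangeable | 3.2e-17 |
| One practice, model-based | 0.331 |
| Patient, robust | 0.331 |
| Ordinary logistic regression | 0.331 |

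The robust figures are zero up to rounding; 0.691/5.5e-17 would be a z statistic of about 1.3e16. The result was the same with a covariate added (independence). The model-based figure equals ordinary logistic regression, so it makes no correction for clustering.

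**4. Does leaving out clinician clustering invalidate the comparison?** The article gives neither the number of clinicians nor an intraclass correlation, so both are assumed here: 5, 10 or 20 clinicians; correlation 0, 0.05 or 0.16; 367 patients randomised individually; a 14% screening rate in both arms; 4,000 simulated trials per setting. Ordinary logistic regression had a type I error of 4.3% to 5.2% throughout. An uncorrected clinician-clustered sandwich had 15% to 17% with 5 clinicians, about 10% with 10 and about 7% with 20. Treatment effects that vary by clinician were not simulated.

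**5. Patients with two outcomes.** 190 + 239 − 367 = 62, or 62/367 = 17%. This sets planning estimates against the accrual count, so it is only rough.

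**The case against.** The strongest defence has three parts.

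First, the article does not say robust or sandwich, and a model-based standard error exists. Because patients are randomised individually, that standard error is sound for the treatment effect. This stands, and it limits the harm. It does not rescue the sentence, since a model-based analysis with one cluster is ordinary logistic regression under another name.

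Second, the phrase may loosely mean clustering by clinician or suite inside the practice; both levels exist. That is possible, but the text does not say it, and a reader could not tell which level is meant. The plural practices mentioned under Role of the community health worker and in the Discussion do not help either, because no second practice is described for the main study.

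Third, a standard error of order 1e-17 would not pass unnoticed into a report. That is fair and lowers the severity.

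Two stronger readings are tempting and are not supported. A reader might infer that ignoring shared clinicians makes the test anti-conservative. With randomisation within clinicians, shared effects fall on both arms and largely cancel, as step 4 of the working shows under its assumptions. A reader might also infer that women due for both tests would be counted as two independent records. The article nowhere says that the two tests are stacked in one model, and it powers them separately. With the practice as cluster, a woman's two records would in any case fall in the same cluster.

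**Conclusion.** The point holds as a contradiction between the analysis section and the site section: the only named model controls for clustering at a level with one member. The usual robust variance is identically zero there, and the model-based alternative adjusts for no clustering. That the sandwich variance was intended is an inference from normal GEE practice, and that the GEE model serves the primary comparison is an inference from its being the only model named.

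The documents do not support saying that the trial cannot produce a valid confidence interval or p-value: an unclustered patient-level analysis does so. Design, data collection and the stated power are unaffected. This should be fixed before analysis but is not a fatal flaw.

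**What to change.** Delete the reference to clustering within practices. Analyse each screening outcome by patient-level logistic regression adjusted for the stratification factor and the covariates already listed. Say how women due for both tests were placed in the strata: within a single-test model, screening type is informative only if those women form their own stratum.

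If some allowance for grouping is wanted, name a level with replicates. The primary care clinician is already in the registry and can enter as a fixed effect, or as the GEE cluster with a small-sample variance correction, because clinicians may be few.

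Only if mammography and colorectal outcomes are modelled jointly, keep both records of a patient in one cluster; roughly 62 patients might then have two.

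The cost is one changed sentence and no new data, plus the small-sample correction if clinician clustering is chosen.

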## Discussion

"Get Screened" is a pragmatic, randomized controlled trial of a multi-modal intervention designed to improve mammography and CRC screening among unselected, low-income patients. This intervention design builds upon prior success in the field of immunization in which multimodal, increasingly intensive interventions improved immunizations across various patient characteristics (e.g. race, ethnicity, and insurance) in safety net practices and decreased disparities. Preliminary data during the pilot study suggest that this multimodal intervention could triple rates of screening in practices with low baseline rates of screening. We hope to confirm these promising findings using a randomized, controlled study design.

Other notable features of the project include patient-level randomization, targeting of safety-net practices, creation of a practice-based registry and a combination of clinician and patient prompts at point-of-care combined with increasingly intensive outreach to unscreened patients.

Key challenges during early stages of implementation have included limitations of the EMR, especially the lack of an electronic alert system that clinicians actually use. The finding that the EMR was poorly designed for tracking preventive health services and providing reminders, led to modification of our alert intervention plan. It also presented an opportunity to populate this portion of the EMR in order to promote future cancer screening tracking within the practice. It is likely that many EMR systems are similarly limited in the degree of practical help they provide clinicians in improving rates of cancer screening.

Another challenge involves developing an efficient system for identifying patients who are screened during the intervention period in order to focus resources on those remaining unscreened. The complex range of CRC screening choices was cited by participating clinicians as a barrier to discussion of screening. This and other feedback from the practice was used during early pilot work to modify and tailor the intervention. One modification was the use of a simplified CRC point-of-care decision-making tool that focused on the choice between colonoscopy and FOBT testing. Findings from this study should inform implementation of cancer screening within safety net primary care practices.
